#### Process evaluation

The purpose of the process evaluation is to establish actual exposure to the intervention as it was intended, and to examine which components of the intervention were successful and which ones were not. The research question is: *To what extent do the nurses adhere to the intervention for CVRM and decision support, and what are the experiences and opinions of the GPs and nurses with regard to this intervention?*

### Variables and measurements

Data on the nurses' actual adherence to the components of the strategy will be gathered by the nurses themselves by means of prospective self-reports. Nurses will use a short standardised questionnaire after each consultation to record which components of the intervention have been applied. Each item will be scored as a done/not done binary variable (see Table 3 for the key intervention features that will be scored). On top of this, each nurse will be instructed to audiotape 3 consultations, namely one of the initial ones and two later on in the trial. In addition to this quantitative approach to process evaluation, we will also use a qualitative approach, in that the nurses will be invited to a focus group interview to discuss their perception of determinants of success and failure. The variation in the effects at the patient and nurse levels will also be discussed. Finally, a subgroup of GPs will be invited for face-to-face interviews about their opinion on the intervention. The sample will include practices with successful as well as less successful patient inclusion. The focus group and the interviews will be moderated by an experienced GP, who is not a member of the research group.

**Table 3 T3:** Key features of the intervention for quantitative process evaluation

**1^**st **^consultation**	Nurse explains the risk to the patient by means of the risk communication tool.
	Nurse hands over the risk communication tool.
	Nurse hands over decision aid booklet + risk communication tool (to consider at home).
**2^**nd **^consultation**	Patient shows up for second consultation. If patients cancel, they are asked for the reason
	Nurse uses motivational interviewing; sets agenda with the help of an agenda-setting chart, establishes importance and confidence, explores importance and builds confidence by asking the patient questions.
	Which options for risk reduction were discussed during the consultation?
	Nurse guides the patient in formulating the main personal goal for lifestyle change (if applicable).
	When medication is prescribed: has the nurse consulted the GP?
	Which other health education materials were used during the consultation?
**Telephone call**	The telephone call takes place. If patients cancel, they are asked for the reason
	Nurse uses motivational interviewing; sets agenda with the help of an agenda-setting chart; establishes importance and confidence, explores importance and builds confidence by asking the patient questions.
	Which options for risk reduction were discussed during the telephone call?
	Nurse guides the patient in formulating the main personal goal for lifestyle change (if applicable).
**Extra items**	Time needed per patient contact.
	Time needed to discuss patients with GP.
	Appointment for follow-up consultation after the telephone call, if necessary.

### Data analyses

The self-reported done/not done components of the intervention will be presented as the proportion of the consultations in which the component has been applied. The audiotaped consultations in the intervention group will be scored with the IMPALA Practice nurses Scoring list (IPS), a scoring list based on the IMPALA training programme and on other existing scoring lists [53,54], to determine the extent to which the motivational interviewing technique was implemented. The consultations will be scored with the OPTION instrument to measure to what extent practice nurses have involved patients in the decision-making process [55,56]. The interviews with the nurses and the GPs will be transcribed and coded by three persons, using a coding list. Differences of opinion will be discussed until agreement is reached.

#### Ethical evaluation

The ethical evaluation will use interviews with individual patients regarding their opinions about and experiences with the consultations of the intervention, to evaluate the intervention in the light of the models of physician-patient relationship by Emanuel and Emanuel [41].

The research question is: *How do patients experience the nurse-led intervention for CVRM, and what is the ethical value of the intervention?*

### Variables and measurements

At least 16 patients of 4 practices will be invited by the nurses to participate in an interview. The 4 nurses implementing the intervention most satisfactorily (judging from the audiotaped consultations), will be asked to invite a variety of patients in terms of sex, 10-year risk of CVD and the course of the consultations.

The interviews will be 'open', in that the interviewer will try to access the patient's personal story. The interviews will be held in the diagnostic style, and will characterised by an interested and personal approach [57]. The interviews will be based on a list of themes to ensure that all relevant items are brought up during the discussion (see Table 4). All interviews will be audiotaped, with the patients' permission, and transcribed later. The interviews will be done by an experienced junior social scientist, who is not a member of the research group.

**Table 4 T4:** Interview themes for ethical evaluation

1. Expectations before the consultations about:	the role of the patient (e.g. active/passive);
	the role of the practice nurse (e.g. guiding, informative, clarifying, reflecting);
	the gain from the consultations (e.g. information, becoming aware, getting attention, reflection and a motivated decision, guiding towards a decision).
2. Experiences with the consultations	Understanding the situation.
	What had the patient picked up from the consultations?
	What was the role of the tools in this understanding?
	How was the patient involved in the consultations?
	Active participation in the discussion.
	Personal involvement in the topic.
	Contribution to the decisions that were made.
	How did the nurse approach the patient (e.g. attentive, open to the patient's opinion, steering, informative, giving his/her own view)?
	What was the impact of the consultation
	for the patient's personal life and well-being;
	as regards clear decisions, goals and a plan?
	The tools of the intervention
	What did the tools mean to the patient?
	Was anything missing from the consultations?
3. Preferences for future consultations:	about the patient's role;
	about role of the practice nurse;
	about the significance of the consultation. When is a consultation successful?

### Data analysis

The interviews will be analysed by the constant comparative method as described in grounded theory [58]. Interviews will be coded and the codes will be grouped, compared and categorised.

#### Economic evaluation

The aim of the economic evaluation is to assess the costs of the IMPALA intervention. The research question is: *What is the incremental cost-effectiveness ratio of a nurse-led intervention for CVRM and decision support compared to usual care by a practice nurse?*

### Measurements and variables

The use of CVD-related health care resources will be measured by means of questions about health care use (prescribed medication, tests, referrals, numbers of contacts) over a 3-month period before completion. Costs of CVD events will be estimated from the literature and/or analyses of aggregate data sources (hospital information systems). Cost calculation will be based on real prices or on unit prices from the Dutch guideline for cost calculation [59]. Quality of life will be measured with the SF-36, a validated questionnaire [60]. The costs of implementing the intervention will be recorded by the researchers.

### Timing of measurements

The questions for the economic evaluation will be incorporated in the questionnaires of the effect evaluation at T0, T1 and T2.

### Data analyses

The economic evaluation will be a cost-effectiveness study. We expect no differences in short-term societal costs because the improvements in lifestyle will mainly have effects in the long term. Therefore, the analyses will use a health care sector perspective, and will thus also show the expected costs and consequences per general practice. The base case involves calculation of an incremental cost-effectiveness ratio (ICER) of patient involvement as regards the estimated reduction of CVD events in 10 years on the basis of T2 data [61]. Quality improvement cost-effectiveness will be combined with treatment cost-effectiveness according to the Mason model [62,63]. Cost differences between the intervention and control groups will be statistically tested by calculating the 2.5 – 97.5 percentile intervals of the bootstrapped resamples.

In addition, we will use a long-term economic evaluation to explicitly reveal the relationship between the CVD risk reduction achieved and the required investment for the implementation strategy. For this purpose, a Markov health state transition model will be developed, with a first-order Monte Carlo simulation in which each patient goes through the model individually. The cycle length will be one year. The time horizon of the analysis is the full lifetime of the population. Costs and benefits will be discounted according to national guidelines (4%). A one-way sensitivity analysis will be used to establish the individual effects of model parameters on the results of the analysis. The model parameters will be varied across a plausible range. Parameter uncertainty will be further tested using probabilistic sensitivity analysis, which takes into account the fact that some combinations of factors are more likely than others [64].

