**Methods:**

A cluster-randomised controlled trial in 20 general practices, 10 practices in the intervention arm and 10 in the control arm, starting on October 2005. A total of 720 patients without existing cardiovascular diseases but eligible for cardiovascular risk assessment will be recruited.

In both arms, the general practitioners and nurses will be trained to apply the national guideline for cardiovascular risk management. Nurses in the intervention arm will receive an extended training in risk assessment, risk communication, the use of a decision aid and adapted motivational interviewing. This communication technique will be used to support the shared decision-making process about risk reduction. The intervention comprises 2 consultations and 1 follow-up telephone call. The nurses in the control arm will give usual care after the risk estimation, according to the national guideline.

Primary outcome measures are self-reported adherence to lifestyle advice and drug treatment. Secondary outcome measures are the patients' perception of risk and their motivation to change their behaviour. The measurements will take place at baseline and after 12 and 52 weeks. Clinical endpoints will not be measured, but the absolute 10-year risk of cardiovascular events will be estimated for each patient from medical records at baseline and after 1 year.

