## Methods

### Design

The IMPALA study is a cluster-randomised controlled trial involving 20 general practices and 720 patients in the Netherlands. An independent statistician will perform a central block randomisation. Practices will be randomly allocated, 10 practices to the intervention group and 10 practices to the control group, after stratification into 4 geographical regions. Assessments will be made at the inclusion of the patients in the study, at 12 weeks and at 52 weeks. A flowchart of the study is shown in Figure 1.

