### Data analysis

Since it is not possible to restrict our study to one primary outcome for all patients beforehand, the study will examine 6 different lifestyle changes: smoking, physical exercise, fat intake, fruit, vegetables and alcohol.

To assess the difference in primary outcomes between the arms, the arms will first be compared in terms of changes in the specific lifestyle issues, independent of the targets chosen by the intervention patients. We will use a T test for continuing variables and a χ^2 ^test for dichotomous variables.

A second analysis of primary outcomes is a multilevel regression analysis (using SPSS and MLwin), which uses adherence to the primary outcomes of lifestyle change as the dependent variables and group allocation and pre-intervention scores as independent variables. Additional independent variables will be included in the model, such as patient characteristics (age, sex, anxiety and risk of CVD). Additional regression analyses will focus on the effect at T2.

The third analysis involves constructing a simple standardised overall adherence score for the six lifestyle items, which expresses to what extent, on average, patients achieved the behaviour change goals of the national recommendations for a healthy lifestyle. The score of the intervention group will be compared with that of the control group.

Finally, the reduction in the 10-year risk of CVD will be analysed for differences between the two arms. The risk of CVD will be analysed with a multilevel regression analysis, which uses the risk at 52 weeks as the dependent variable and group allocation and pre-intervention risk as independent variables.

The secondary outcomes will also be analysed for the differences between the arms, using a T test for continuing variables and a χ^2 ^test for dichotomous variables. We also intend to use a multilevel regression analysis (using MLwin) which uses e.g. self-efficacy and attitudes at T1 as the dependent variables and group allocation and pre-intervention scores as independent variables. Additional independent variables, such as patient characteristics (age, gender, risk of CVD and socio-economic status), will also be included in the model. Additional regression analyses will focus on the effect at T2. Further analyses for subgroups of patients are also possible.

In addition, we will describe the personal targets of the patients in the intervention arm, which will be recorded by the nurses.

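### The planned test of the between-arm cost difference names no adjustment for the baseline health-care use that the trial collects

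*Protocol article*

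**What the plan says.** The cost comparison is given in one sentence of the protocol article (Economic evaluation, Data analyses): "Cost differences between the intervention and control groups will be statistically tested by calculating the 2.5 – 97.5 percentile intervals of the bootstrapped resamples". No covariate and no resampling unit is named.

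Baseline costs will be available. Health-care use is asked "over a 3-month period before completion" of each questionnaire (Economic evaluation, Measurements and variables), and "The questions for the economic evaluation will be incorporated in the questionnaires of the effect evaluation at T0, T1 and T2" (Economic evaluation, Timing of measurements). The T0 questionnaire is filled in before the first consultation (Effect evaluation, Timing of measurements), so its recall window precedes the intervention. The article gives these T0 cost answers no stated role in any analysis.

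The effect evaluation does use baseline values. Its multilevel models for primary and secondary outcomes include pre-intervention scores, and its model for 10-year CVD risk is one "which uses the risk at 52 weeks as the dependent variable and group allocation and pre-intervention risk as independent variables" (Effect evaluation, Data analysis).

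The ICER's effect term is described only "as regards the estimated reduction of CVD events in 10 years on the basis of T2 data" (Economic evaluation, Data analyses).

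**The concern.** Eligible patients range from smokers without other listed risk factors to people already treated for hypertension or high cholesterol and people with diabetes (Participants). Their earlier use of care plausibly predicts their later use. Only 20 practices are randomised, so mean prior use can differ between arms by chance. An unadjusted comparison carries part of that difference into the estimated cost of the intervention.

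The cost difference is the numerator of the ratio that answers research question 4. If prior use predicts later use, leaving out a variable that is already collected gives a less precise estimate than the data allow. The article states baseline adjustment for its other outcomes, so the absence of a baseline term for costs stands out.

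**Working it through.** The article gives no standard deviation, correlation, ICC or power for costs, so there is no figure of its own to reproduce here. The calculation below is illustrative and in SD units.

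**Inputs from the article**
- 20 practices, with "10 practices to the intervention group and 10 practices to the control group, after stratification into 4 geographical regions" (Design).
- 600 patients at 52 weeks, 300 per arm (Sample size calculation), hence 300/10 = 30 per practice.
- ICC 0.04, stated for adherence (Sample size calculation).

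**Assumptions**
- The same ICC applies to baseline cost; 0.01 to 0.10 is shown as a range.
- The correlation r between T0 and follow-up cost is not given; 0.3, 0.5 and 0.7 are shown. It is taken to be the same within and between practices.
- Any gain from stratifying by region is ignored.

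**Step 1. Chance baseline imbalance**
- Design effect = 1 + (30 − 1) × 0.04 = 2.16.
- SE of the baseline difference between arms = √(2 × 2.16/300) = 0.12 SD.
- 95% range = ±1.96 × 0.12 = ±0.235, about ±0.24 SD.
- ICC 0.01: design effect 1.29, SE 0.093, range ±0.18 SD.
- ICC 0.10: design effect 3.90, SE 0.161, range ±0.32 SD.

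**Step 2. Part that enters an unadjusted follow-up difference**

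A baseline difference d contributes r × d. At the edge of the 95% range (0.235 SD):
- r = 0.3: 0.07 SD
- r = 0.5: 0.12 SD
- r = 0.7: 0.16 SD

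**Step 3. Interval width, adjusted relative to unadjusted, same resampling scheme**

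The ratio is √(1 − r²):
- r = 0.3: 0.954, about 5% narrower
- r = 0.5: 0.866, about 13% narrower
- r = 0.7: 0.714, about 29% narrower

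**Step 4. Why a covariate and not a subtracted baseline**

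The width of a change-score interval relative to the unadjusted one is √(2(1 − r)). At r = 0.3 this is 1.18, so subtraction would widen the interval. At r = 0.5 it is 1.00, no gain. Regression on T0 cost does not have this drawback.

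**Step 5. Why the resampling unit must be settled in the same sentence**

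If patients and not practices were resampled, the interval would be too short by a factor √2.16 = 1.47 at ICC 0.04. An unadjusted patient-level interval would then have 1/1.47 = 0.68 of the width of a correct unadjusted one. It would be shorter than the correct adjusted interval unless √(1 − r²) < 0.68, that is, unless r exceeds about 0.73. The gains in step 3 therefore hold only when both intervals come from the same resampling scheme.

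**The case against.** The strongest reply is that the sentence names an interval method, not the statistic being resampled. A condensed article may leave covariates to a fuller plan, and asking about costs at T0 could itself signal an intended baseline use. This stands in part: the article does not say that the difference is unadjusted. But it does name baseline adjustment for its other regression models, and for costs it describes a different method without one. Adding the covariate improves on the method as stated.

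Several stronger readings are tempting, and the article does not support them.

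- *The ICER's effect term ignores baseline risk.* A reader might infer this from the reference to T2 data. But 10-year risk is estimated at both time points ("the absolute 10-year risk of cardiovascular events will be estimated for each patient from medical records at baseline and after 1 year"), and the effect evaluation analyses its reduction with pre-intervention risk in the model. The ICER wording can naturally be read as taking that estimate.
- *The ICER's interval is too wide.* The percentile interval is stated for the cost difference. None is stated for the base-case ICER.
- *The cost interval is certainly wider than needed.* The resampling unit is not stated, and a patient-level bootstrap would err in the other direction (step 5).
- *The cost result is biased.* Chance imbalance under randomisation is sampling error, which an interval that respects clustering covers. A reader might suspect arm-dependent recruitment because practice staff enrol the patients, but the article reports no such difference and this point does not rest on one.
- *A known amount of power is lost.* The 80% power in the article is for adherence; no cost contrast is powered.

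Two further limits stand. Implementation costs, recorded by the researchers, have no T0 counterpart, so baseline use cannot explain any variance they add. The ICER also follows a published model that combines quality-improvement with treatment cost-effectiveness; changing how the patient-level cost difference is estimated need not alter that structure.

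**Conclusion.** The point holds for the cost comparison. Pre-intervention health-care use is collected, the stated cost test names no baseline term, and the effect evaluation shows that baseline adjustment is otherwise part of the plan. The consequence is lost precision in a non-primary evaluation, with a chance baseline imbalance of about ±0.24 SD inside the 95% range (±0.18 to ±0.32 SD over the ICC range shown).

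The gain of about 5% to 29% in interval width rests on assumed correlations of 0.3 to 0.7, on a borrowed ICC, and on the same resampling scheme for both intervals. It shrinks to the extent that implementation costs add variance. For the effect term, only a clarification is warranted.

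**What to change.** In the Data analyses section of the Economic evaluation:

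1. State that in each bootstrap resample the cost difference is the allocation coefficient from a regression of follow-up cost on allocation and T0 cost.
2. State that whole practices are resampled, so that the interval respects the clustering.
3. Report the unadjusted cost difference, from the same resamples, as a sensitivity analysis.
4. State that the ICER's effect term is the baseline-adjusted 52-week risk difference from the effect evaluation.

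This costs a few sentences and a small change to the bootstrap code, with no new data. The one downside is that patients with missing T0 cost answers need an imputed baseline value to stay in the analysis, and the rule for that should be fixed in advance.

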## Discussion

The intervention that will be evaluated in this trial is characterised by some innovative aspects. Firstly, not much is known yet on the effect of the combined use of risk communication, a decision aid and motivational interviewing to enhance patient involvement in decision making. Secondly, delegation of such tasks to a practice nurse is a new approach in the Netherlands, and is in line with current changes in general practice care processes in this country (increasing practice sizes and multidisciplinary health centres employing nurses).

A factorial or multiple-arm RCT design would have been optimal from the methodological perspective, and could shed light on the effectiveness of the individual ingredients of this multifaceted intervention in terms of the primary outcomes. However, this would have blown up the design to include multiple trial arms and large numbers of practices and patients, and turn it into an unfeasible experiment. The analyses of our secondary outcomes will probably shed light on the effectiveness of individual ingredients of the intervention. In some of the secondary outcomes, such as risk perception, the relation with individual ingredients, such as risk communication, seems one-dimensional. The way in which risk communication, the decision aid and motivational interviewing are applied during the trial will be documented in a process evaluation, which will give further information on the impact of intervention components on the main outcomes.

The pilot version of the risk communication tool included a Paling scale, a scale to compare the risk of cardiovascular risk with other risks of life. After the pilot test, we decided to remove the Paling scale because it was too difficult according to the patients who received the risk communication tool in this pilot test.

When we developed the decision aid, the IPDAS criteria for decision aids had not yet been published [65], but the decision aid does comply with most of the these criteria, namely using a systematic development process, providing information about options, presenting probabilities, disclosing conflicts of interests and using plain language. On the other hand, our decision aid does not fully meet the criteria on balancing the presentation of options, clarifying and expressing values, and guiding/coaching in deliberation and communication, although patients will be invited to deliberate about the decision making, and the motivational interviewing in our strategy is meant to help patients clarify and express values.

Cardiovascular risk is not the primary outcome of the effect evaluation because this is a pragmatic trial about the implementation of the Dutch national guideline for CVRM. To reduce the burden of data collection for the health care professionals, we will ask them to collect only the data they need for the risk estimations. There is no budget for additional data collection outside routine practice by the researchers.

Although we intended to use more objective measures for the primary outcomes of the effect evaluation, this was precluded by logistic and financial reasons. The relatively inexpensive breath carbon monoxide test is not very sensitive, and the more reliable urine cotinine marker is expensive and difficult from a logistic point of view. A biomarker for fruit and vegetables, such as carotene measurement, is expensive, and no simple biomarker for alcohol is available. The influence of information bias resulting from subjective self-reports is reduced in the data analysis, which takes the pre-intervention scores (which have the same information bias) into account. Although self-reported smoking status is known to be biased, measurement of a biological marker has various disadvantages.

